## Background

Electrical status epilepticus in sleep (ESES) was initially described as a subclinical electroencephalographic (EEG) pattern of sleep-induced spikes and waves (SWs) in children, occupying 85–100% of slow wave sleep [1]. When bilateral ESES is associated with cognitive decline or behavioural disturbances, a diagnosis of encephalopathy with ESES can be made. The cognitive deficits are global (often referred to as continuous spikes and waves syndrome, CSWS) or confined to a specific cognitive domain (e.g. acquired aphasia or auditory agnosia in children with Landau-Kleffner syndrome, LKS) [2, 3]. These phenotypes are referred to as “typical ESES patients” [4, 5]. The exact incidence of the epileptic encephalopathy with ESES is unknown, but it is estimated to constitute 0.2–1.9% of paediatric epilepsy cases [5, 6].

ESES spectrum variants are increasingly recognised and include children with ESES and developmental delay but without arrest or regression of development [7]. Also, the spike wave index (SWI) threshold to diagnose ESES can be flexible, and can be < 85%, provided that the main feature of epileptic encephalopathy with ESES, i.e. occurrence of cognitive and behavioural deterioration associated with a striking enhancement of epileptic activity during NREM sleep, is demonstrated [8]. How ESES causes cognitive deficits and which factors determine cognitive outcome remain largely unknown. It has been suggested that ESES disrupts synaptic homeostasis, i.e. the balanced synaptic potentiation during daytime and synaptic downscaling in sleep, leading to an inefficient cerebral network [9]. Epileptic encephalopathy with ESES has been reported in patients with structural abnormalities (e.g. perinatal thalamic injury) [10, 11] and genetic disorders (e.g. a GRIN2A mutation) [12, 13], though in about half of the cases no clear cause is identified. Evidence is accumulating for a role of the immune system in patients with epilepsy [14]. In children with Landau-Kleffner syndrome, autoantibodies to central and peripheral myelin, cell nucleus, and blood vessels in sera and cerebrospinal fluid have been found [15]. In addition, in a previous study, we found that several cytokines were significantly higher in blood samples of patients with encephalopathy with ESES compared with healthy controls [16].

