Whilst the EEG abnormalities characteristic of ESES generally resolve spontaneously during puberty, cognitive deficits often remain [17, 18]. Treatment during the active ESES phase may improve EEG abnormalities and daily functioning [19, 20]. In fact, successful early treatment (and thereby a shorter ESES duration) is associated with improvement of long-term cognitive outcome [18, 21]. However, the management of encephalopathy with ESES is often challenging and there is no consensus on which is the best initial treatment [22]. Moreover, no adequately powered randomised controlled trials have been performed in children with encephalopathy with ESES.

We recently performed a pooled analysis of 950 treatments in 575 cases with encephalopathy with ESES, reported in 112 articles. Conventional anti-epileptic drugs, often prescribed to control concomitantly occurring epileptic seizures, were generally not very effective in treating ESES and its associated cognitive deficits (improvement of EEG or cognition in 49%). Benzodiazepines and corticosteroids seemed to be more effective, with improvement in 68% and 81% of cases, respectively. However, in a subgroup analysis that included only consecutively assessed patients, a smaller proportion showed any improvement (34% with conventional anti-epileptic drugs, 59% with benzodiazepines, and 75% with corticosteroids). A subgroup of patients with a focal structural abnormality benefitted from epilepsy surgery. These results have to be interpreted with caution because most included studies were small, retrospective, and heterogeneous, and side effects were not considered [19].

Review articles on the treatment of encephalopathy with ESES concluded that no standard approach exists and mentioned high-dose benzodiazepines and (cortico) steroids as preferred options [5, 6, 23]. Among benzodiazepines, clobazam is often considered the most suitable although sedation and agitation are frequent side effects. Corticosteroids have been given in variable dosing regimens, and concerns for side effects such as weight gain and increased blood glucose may be a reason to consider them as a second-line option. All authors emphasise that the evidence guiding the treatment of encephalopathy with ESES is unsatisfactory, and therefore, a randomised controlled trial is urgently needed.

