We hypothesise that, in comparison to treatment with clobazam, corticosteroids are more effective in improving cognitive performance and EEG abnormalities in children with encephalopathy with ESES. Based on previous studies, the difference in percentage of responders is estimated at around 25% [19]. The use of corticosteroids may be associated with more frequent or more severe side effects than clobazam.

In a multicentre randomised controlled trial with 1:1 allocation to corticosteroids and clobazam, we aim to assess whether one of the treatments is superior to the other. The following study objectives and hypotheses are addressed in a population of recently diagnosed patients with encephalopathy with ESES:

*Primary study objective*
To compare the effects of treatment with corticosteroids or clobazam on cognition at 6 months after start of the treatment.

*Secondary study objectives*
To compare the effects of treatment with corticosteroids or clobazam on sleep-induced epileptiform activity, measured as the spike wave index (SWI), in the patients’ sleep EEG.To compare the effects of treatment with corticosteroids or clobazam on the frequency of any concomitant seizures.To compare the side effects and tolerability of corticosteroids and clobazam.To compare the effects of treatment with corticosteroids and clobazam on subjective daily functioning, as measured with a visual analogue score (VAS).To assess demographic and disease-related biomarkers, including immunological biomarkers, as potential predictors of disease activity and response to treatment with corticosteroids or clobazam.

The study is conducted as a randomised open-label parallel-group controlled trial with 1:1 treatment allocation to clobazam and corticosteroid treatment arms and is aimed at proving superiority of one treatment over the other. The trial also uses a pragmatic approach, whereby participating investigators will be allowed to apply, within predetermined limits, the dosing schedules which they consider best according to their judgement and patient response. The same flexibility will also apply to the option of using i.v. versus oral steroids, which will be left to the discretion of the treating physicians.

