#### Inclusion criteria

Age at inclusion, 2 up to 12 years.A diagnosis within 6 months prior to enrolment (preferably as close to enrolment as possible) of either:
Bilateral sleep-induced epileptiform activity with an SWI > 85% in non-REM sleep and developmental delay, arrest, or regression (“typical epileptic encephalopathy with ESES”).Arrest or regression of development and bilateral sleep-induced epileptiform activity with an SWI > 50%, or unilateral sleep-induced epileptiform activity with an SWI > 85% in non-REM sleep (“atypical epileptic encephalopathy with ESES”).Regression of development and unilateral epileptiform activity with an SWI > 50% in non-REM sleep (“atypical epileptic encephalopathy with ESES”).No previous treatment with either corticosteroids or clobazam.No current treatment, nor treatment in the previous 3 months, with carbamazepine, oxcarbazepine, vigabatrin, tiagabine, gabapentin, and pregabalin. These drugs potentially increase the SWI during sleep and may cause an electrographic pattern fulfilling the criteria for ESES and subsequently worsen outcome in children with epileptic encephalopathy with ESES and may thereby influence treatment results. Therefore, inclusion of such cases with possible “treatment-induced ESES” is not desirable.Written informed consent by parents/legal representatives.

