### Data collection

All patient data for the study will be recorded in the online case report form (CRF) with reference to the patient study number, in compliance with Good Clinical Practice guidelines. Data will be stored in a secure data platform, managed by an independent data manager. The forms were created by the study coordinator ([name]) and the principal investigator ([name]) and reviewed by the steering committee. Data quality and completeness will be checked by the study monitors, who will be granted access to the online CRF and the hospital (electronic) medical records of the included patients for the duration of their monitoring activities.

*Baseline data (t = 0 months)* will be collected before treatment initiation and include patient demographics, date of ESES diagnosis, onset of ESES, seizure type(s), anti-epileptic drug history, detailed history of psychomotor development and behaviour, estimated age at onset of developmental arrest or regression, impression of global functioning assessed with VAS score (− 5 to 5), and neurological examination. Ancillary investigations related to aetiology will be reassessed or scheduled (if not yet performed) and will include a cerebral MRI (dedicated epilepsy protocol) and genetic tests if no aetiology is known (array CGH, mutation analysis including GRIN2A gene). Metabolic screening and a cerebrospinal fluid tap will be performed if considered indicated.

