### Statistical analysis

The primary analyses will be performed according to the intention-to-treat principle. We will also perform (secondary) analyses in patients who have completed their assigned treatment for the period of 6 months.

Continuous outcomes will be presented with means and 95% confidence intervals. These outcomes will primarily be compared between the two treatment groups using a *t* test or Mann-Whitney *U* test depending on the distribution of the data (normal vs not normal). Categorical outcomes will be presented as proportions with 95% confidence intervals. These outcomes will primarily be compared between the two treatment groups using Fisher’s exact test. Rates of (serious) adverse events will be compared in terms of risk ratios with corresponding 95% confidence intervals. We will also identify the proportion of patients that continue on the initially allocated treatment throughout the entire study period, and analyse possible predictors for discontinuation.

Although the stratified randomisation procedure intends to create two groups with equal patient characteristics, it is known that in randomised trials of < 1000 patients, there still is a risk of bias by chance [25]. Adjusted analyses are often performed to reduce the influence of the possible differences between the two treatment arms [26]. Therefore, possible predictors of treatment outcome (i.e. known prognostic factors) will be included in a multivariate logistic/linear regression model. These prognostic factors are as follows: age at ESES recording, time interval between ESES recording and inclusion, IQ levels and cognitive sum scores at enrolment, number of drugs administered before enrolment, and aetiology (unknown, structural, metabolic, genetic, immune, infectious). We will also include cytokine and autoantibody profiles as possible predictors.

The prospective design and structured follow-up schedule should minimise the amount of missing data. However, to account for possible influence of missing data, we will perform a sensitivity analysis using multiple imputation methods [27].

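### The adjusted model leaves out pre-enrolment ESES duration, although onset is recorded at baseline, and its recording-to-inclusion interval is probably a weak proxy for it

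*Protocol article*

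**What the plan says.** All references are to the protocol article.

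- **Inclusion criteria.** Entry requires "A diagnosis within 6 months prior to enrolment (preferably as close to enrolment as possible) of either" of the listed EEG and developmental patterns. The age criterion is "Age at inclusion, 2 up to 12 years". Neither the inclusion nor the exclusion criteria limit time since ESES onset. The Background describes the objectives as pursued "in a population of recently diagnosed patients with encephalopathy with ESES".
- **Background.** The protocol states that "successful early treatment (and thereby a shorter ESES duration) is associated with improvement of long-term cognitive outcome". It also states: "How ESES causes cognitive deficits and which factors determine cognitive outcome remain largely unknown".
- **Data collection.** The baseline items include "date of ESES diagnosis, onset of ESES" as separate entries, and also an estimated age at which developmental arrest or regression began.
- **Statistical analysis.** The main between-group comparisons are unadjusted (t test or Mann-Whitney U test, and Fisher's exact test). Because chance imbalance is possible in a trial of this size, a regression model with listed prognostic factors follows. The timing factors are "age at ESES recording, time interval between ESES recording and inclusion". The others are baseline IQ and cognitive sum score, number of earlier drugs, and aetiology, with cytokine and autoantibody profiles as further possible predictors. Multiple imputation is planned as a sensitivity analysis for missing data.

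**The concern.** Eligibility counts from diagnosis, not from onset. A child with years of unrecognised ESES and a child with weeks of it can both enter shortly after diagnosis, and both would have a short recording-to-inclusion interval. The variation in how long the disease had been active before treatment lies mainly in the lag from onset to recording, and the listed interval does not see that lag.

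Age at recording does not fill the gap. It is age at onset plus the lag, so it cannot separate early onset with late diagnosis from late onset with prompt diagnosis.

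The section's stated reason for adjusting is to reduce the influence of chance differences between arms. Duration is the time-related factor that the Background ties to cognition, and an imbalance in it would be handled only as far as the other covariates happen to carry it. The same list is the set of possible predictors of outcome, so duration is absent from that prespecified model too.

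**Working it through.** **The plan's own figure.** For 50% versus 25%, two-sided 5%, 80% power, pooled variance and no continuity correction:

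n per arm = [1.960·√(2·0.375·0.625) + 0.842·√(0.50·0.50 + 0.25·0.75)]² / 0.25² = (1.342 + 0.557)² / 0.0625 ≈ 57.7, so 58 per arm and 116 in total, as stated. Then 116/0.9 = 128.9, or 129, against 130 planned. The point below changes none of this.

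**Step 1: spread of the listed interval.** Input: a 6-month limit (Inclusion criteria), taking the ESES recording to be the diagnostic EEG.

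- Uniform on 0 to 6 months: SD = 6/√12 = 1.73 months.
- Largest possible (half the children at 0, half at 6): SD = 3 months.
- Clustered near enrolment, as the criterion prefers: SD = 1 month, assumed.

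**Step 2: how much of pre-enrolment duration the interval carries.** Write duration = L + I, where L is the lag from onset to recording and I is the interval, assumed independent. Then R² = SD(I)² / [SD(I)² + SD(L)²]. The documents give no SD for L, so a range is assumed.

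| Assumed SD of L (months) | SD(I) = 1 | SD(I) = 1.73 (uniform) | SD(I) = 3 (maximum) |
|---|---|---|---|
| 3 | 10% | 25% | 50% |
| 6 | 2.7% | 7.7% | 20% |
| 12 | 0.7% | 2.0% | 5.9% |
| 24 | 0.2% | 0.5% | 1.5% |

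Worked example, uniform interval and SD(L) = 6: 3/(3 + 36) = 7.7%.

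**Step 3: chance imbalance.** With 65 per arm, the standard error of a standardised baseline difference is √(2/65) = 0.175, and 1.96 × 0.175 = 0.34. An imbalance in duration of about 0.34 SD or more, in either direction, is expected in 5% of trials. This holds for any baseline variable at this size. What it would do to the treatment estimate depends on the slope of outcome on duration, which the documents do not give.

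**The case against.** Much can be said for the plan, and several stronger readings fail.

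- **That the protocol names pre-enrolment duration as prognostic.** A reader might infer this from the Background, but that sentence concerns total duration, as shortened by successful treatment, and long-term outcome. It says nothing about duration before enrolment and the 6-month endpoint, and the same section says the determinants of outcome are largely unknown. What stands is that pre-enrolment duration is the part of total duration already fixed at randomisation, and so the part that can serve as a baseline covariate.
- **That the interval is almost constant, or carries at most about 1% of the variance in duration.** The documents do not support either. The interval can vary over 6 months, and the assumed inputs above give 0.2% to 50%. Nor is the recording defined: diagnosis also needs developmental criteria, so a first ESES EEG could precede it and the interval could exceed 6 months.
- **That the eligibility rule is an error.** It is not. A recently diagnosed population and a limit on time since diagnosis agree with each other.
- **That the primary result is compromised.** It is not. The main comparison is unadjusted, and randomisation with the test's error rate covers chance imbalance in unlisted factors. Baseline IQ and sum score may also carry part of any effect of earlier disease.
- **That the predictor objective cannot examine duration.** Nothing bars it, since onset is in the case report form. Duration is only missing from the prespecified list.
- **That the interval should be replaced outright.** An EEG date is objective, whereas ESES onset is partly estimated. Onset of arrest or regression is no general substitute, because children with developmental delay alone are eligible. This objection stands, and it argues for adding duration and keeping the interval.

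**Conclusion.** The point holds in limited form. The protocol itself fixes the covariate list, and that list omits a baseline quantity which the Background makes plausible as prognostic and which is already collected. The listed interval is range-restricted if the recording is the diagnostic EEG. It is then a weak proxy for pre-enrolment duration when the onset-to-recording lag has an SD of 6 months or more: R² is about 8% or less with a uniform interval, and up to 20% at the extreme interval SD of 3 months. If the lag varies by only about 3 months, the interval is a fair partial proxy (25% when uniform) and the gain from adding duration is smaller.

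These figures rest on an assumed lag SD, on independence of lag and interval, and on the diagnostic-EEG reading. The consequence is confined to the adjusted estimates at 6 and 18 months and to the predictor model. The 18-month estimates are where the Background's long-term association bears most directly. Sample size, power and the validity of the unadjusted primary test are unaffected.

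**What to change.** In the Statistical analysis section:

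1. Add time from ESES onset to randomisation, from the baseline onset item, to the listed prognostic factors, and keep the recording-to-inclusion interval beside it.
2. State which EEG is the ESES recording: the first that showed ESES, the diagnostic EEG, or the whole-night recording required before randomisation.
3. Where onset is unknown, use the multiple imputation already planned for missing data. Do not substitute onset of arrest or regression, which is undefined for children with delay only.

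The cost is a few lines of wording and one extra model parameter. No new data are needed and the sample size does not change. The drawback is that onset is partly estimated from history, so the covariate carries measurement error and will correct an imbalance in duration only in part.

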### Outcomes

The co-primary outcome measures at 6 months will be cognitive functioning, assessed with a full neuropsychological assessment (NPA):
Intelligence quotient (IQ), or developmental quotient (DQ), compared to baseline IQ/DQ. Improvement is defined as an increase by 10 IQ/DQ points.Cognitive sum score (as defined below). Improvement is defined as statistically significant when improved by at least 75% of the standard deviation (SD).

Secondary outcome measures at 6 and 18 months will include the following:
Changes in individual absolute test results, and IQ/DQ scores, compared to baseline.Changes in spike wave index (SWI) during non-REM sleep, compared with baseline SWI.Changes in seizure frequency assessed for all reported seizure types combined, with improvement being defined as at least 50% decrease as compared with baseline.Changes in subjective global daily functioning assessed with a visual analogue score (VAS) of − 5 to + 5 as compared with baseline.Safety and tolerability, as assessed by the occurrence of adverse events.Change in inflammatory markers post-treatment as compared to levels prior to treatment.Identification of autoantibodies as potential biomarkers of disease severity (TIQ, presence of developmental regression, arrest, or delay and SWI at baseline) and treatment efficacy.

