### Neuropsychological assessment at baseline, after 6 months, and after 18 months

Depending on the age and abilities of the patient, tests will be selected from a fixed battery covering the major domains of cognition (intelligence, language, memory, attention, visuospatial functions, executive functions, as specified in an appendix of the study protocol). Administration and scoring will be conducted according to the test manuals. Individual raw test scores at baseline and at follow-up will be transformed into *z*-scores, based on the mean and SD of standard scores. As a measure of overall cognitive functioning, a cognitive sum score will be calculated, representing the mean *z*-score over the 6 domains. Neuropsychologists will be blinded to treatment.

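### The fixed covariate list leaves each secondary outcome's own baseline value (notably SWI) out of its adjusted model, and leaves developmental course out of all of them

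*Protocol article*

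**What the plan says.** The Statistical analysis section of the protocol article makes the unadjusted comparisons primary: Fisher's exact test, t test or Mann-Whitney. It then says that chance differences between arms remain possible at this trial size and plans adjusted logistic or linear models to reduce their influence. The covariates are enumerated: "These prognostic factors are as follows: age at ESES recording, time interval between ESES recording and inclusion", followed by "IQ levels and cognitive sum scores at enrolment, number of drugs administered before enrolment, and aetiology (unknown, structural, metabolic, genetic, immune, infectious"). The one stated addition is "We will also include cytokine and autoantibody profiles as possible predictors".

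Other sections bear on that list:

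- **Outcomes** defines SWI, VAS and seizure frequency as changes from baseline. In the autoantibody outcome it also describes "disease severity (TIQ, presence of developmental regression, arrest, or delay and SWI at baseline) and treatment efficacy".
- **Inclusion criteria** admit a wide mix, for example "Arrest or regression of development and bilateral sleep-induced epileptiform activity with an SWI > 50"%. Children with delay alone can enter only with bilateral SWI above 85%.
- **Treatment** stratifies randomisation by centre only.
- **Background** lists the objective "To assess demographic and disease-related biomarkers, including immunological biomarkers, as potential predictors of disease activity and response to treatment".
- **Neuropsychological assessment** builds the sum score from six domains, "covering the major domains of cognition (intelligence, language, memory, attention, visuospatial functions, executive functions", so intelligence is one of its components.

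**The concern.** The list is introduced as complete and serves all outcomes, yet it is built around cognition. It carries both cognitive baselines into every model and carries no baseline for SWI, VAS or seizure frequency. A change score subtracts the baseline but does not adjust for it. How far SWI can fall depends on where the child starts: about 50 points for a child entering just above 50%, and up to 100 points for one entering at 100%. A chance difference in starting SWI therefore passes into the adjusted SWI comparison, and the precision that the baseline could supply is lost.

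Developmental course varies by design of the eligibility criteria and is balanced by nothing except chance. As listed, the models cannot correct for an imbalance in it, and it cannot appear as a predictor of response. What is at stake is the quality of the supportive adjusted and predictor analyses.

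**Working it through.** **1. The plan's own figure.** For 50% versus 25%, two-sided 5% and 80% power, the pooled-variance formula without continuity correction gives 58 per arm, or 116. Dividing by 0.90 gives 129, against the 130 stated. The figure reproduces, and the calculations below use 58 evaluable children per arm.

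**2. What the list contains.**

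| Baseline variable | In the list? | Where it is available |
|---|---|---|
| IQ/DQ | yes | baseline neuropsychological assessment |
| Cognitive sum score | yes | same |
| SWI | no | whole-night EEG before randomisation |
| VAS | no | baseline data |
| Seizure frequency | no | implied by the outcome, which compares with baseline |
| Developmental course | no | eligibility and baseline developmental history |

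**3. Chance imbalance in SWI.** The standardised difference between arms has standard error √(2/58) = 0.186. The probability that it exceeds 0.2 SD is 28%, and that it exceeds 0.3 SD is 11%.

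**4. Gain from conditioning on baseline SWI.** The documents give no correlation between baseline and follow-up SWI, so two assumed patterns bracket the gain.

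- *Equal variances, correlation ρ.* The variance of the change is 2σ²(1−ρ). After adjustment it is σ²(1−ρ²). The ratio is (1+ρ)/2, which is 0.65 at ρ = 0.3 and 0.75 at ρ = 0.5, a reduction of 35% and 25%. Under the same pattern a baseline imbalance of Δ shifts the difference in change by (1−ρ)Δ. At Δ = 0.3 SD this is 0.7 × 0.3 = 0.21 SD or 0.5 × 0.3 = 0.15 SD.
- *Responder pattern.* Responders fall to an SWI of 0–40% and the others stay near baseline, with 40–80% of children entering above 85% and response 50% versus 25%. Simulation (117 children, 3000 runs) gives a variance ratio of 0.955–0.983, a reduction of about 2–5%.

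**5. Developmental course and the success difference.** Two assumptions are needed, neither given in the documents: 20–40% of children have delay only, and success is 15–30 points lower in them. The SD of imbalance is √(p(1−p) × 2/58).

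| Delay-only share p | SD of imbalance | P(imbalance > 10 points) | Shift at 2 SD, gap 15 | Shift at 2 SD, gap 30 |
|---|---|---|---|---|
| 0.20 | 7.4 points | 18% | 2.2 points | 4.5 points |
| 0.30 | 8.5 points | 24% | 2.6 points | 5.1 points |
| 0.40 | 9.1 points | 27% | 2.7 points | 5.5 points |

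The planned difference is 25 points. These shifts give no credit for baseline IQ and sum score, which are in the model and may absorb part of the imbalance.

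**6. Room in the model.** As listed, the logistic model has 11 parameters: treatment 1, age 1, interval 1, IQ 1, sum score 1, prior drugs 1, aetiology 5. Expected responders are 58 × 0.50 + 58 × 0.25 = 43.5, so there are 43.5/11 = 4.0 events per parameter before any cytokine term. Keeping only one cognitive baseline gives 10 parameters (4.35). Adding a binary course term returns to 11 (4.0), and adding SWI as well gives 12 (3.6). Keeping both cognitive baselines and adding SWI plus a three-level course gives 14 (3.1).

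**7. Overlap of the two cognitive baselines.** If the six domains correlate 0.5 with each other (assumed), the correlation of one domain with the mean of all six is √(3.5/6) = 0.76. Entering both spends a parameter on largely shared information.

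**The case against.** The strongest reply is that this is a covariate choice in a supportive analysis, and four parts of it stand.

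- **The primary tests are unadjusted.** A reader might infer that the omission biases the primary result. It does not: the error rate of a randomised comparison already allows for chance imbalance.
- **The severity wording belongs to the autoantibody outcome.** A reader might infer that the protocol names SWI and developmental course as severity measures and then contradicts itself by leaving them out. That passage says what autoantibodies will be related to. The adjusted models rest on a different criterion, known prognostic factors, and no section says that either variable predicts response at 6 months. The Background says the determinants of cognitive outcome are largely unknown.
- **The predictor objective is not defeated.** It names neither variable, and age, interval, aetiology, baseline cognition, cytokines and autoantibodies all serve it. Only these two factors go untested.
- **The model is crowded.** At about 4 events per parameter, leaving out a factor of unproven prognostic value is defensible. Adding developmental course is therefore discretionary.

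Two parts of the reply do not stand. Defining SWI as a change from baseline is not adjustment for baseline, as step 4 shows. Nor can the matter be set aside as detail left to a fuller document: the article chose to enumerate the covariates, and the list as written excludes these baselines.

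**Conclusion.** The point holds in a limited form. The enumerated list omits the outcome's own baseline from the adjusted SWI, VAS and seizure models, and it omits developmental course from all models. The validity of the primary tests and the sample size are untouched.

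The gain for SWI runs from small (2–5% of variance) to material (25–35%), depending on an unknown relation between baseline and follow-up. For developmental course, even a 2-SD imbalance, which about 1 trial in 20 would reach or exceed, shifts the success difference by only about 2–5 points under assumed inputs. The case for own-baseline adjustment is firm because it uses data the outcomes already require and costs almost nothing. The case for adding developmental course is a reasonable option and no more.

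**What to change.** Amend the covariate sentence in Statistical analysis so that each adjusted model includes the baseline value of its own outcome: SWI for SWI, VAS for VAS, seizure frequency for seizures, IQ/DQ for IQ/DQ, and sum score for sum score. State that IQ and the sum score are not entered together.

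Optionally, use the freed parameter to add developmental course as one binary term (delay only versus arrest or regression) in the cognitive models, and examine baseline SWI as a predictor of response.

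**Cost:** a sentence or two, with no new assessments. In the SWI, VAS and seizure models the own-baseline term takes the place of the dropped cognitive baseline, so the count stays at 11. In the cognitive models the core change lowers it to 10, and both optional terms bring it to 12, or 3.6 events per parameter. The drawback is those one or two extra terms in an already crowded logistic model. The change should be fixed before outcome data are examined by arm.
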